Recent studies revealed that in addition to BTK, ibrutinib can also specifically inhibit IL-2-inducible kinase (ITK). Ibrutinib irreversibly binds to ITK and inhibits Th2 cell differentiation and activation[.^27^](#_bookmark46)[^,28^](#_bookmark47) Given the redundant role of resting lymphocyte kinase (RLK) to ITK in Th1 and CD8 T-cells, inhibition of ITK provides a platform for preferential activation of Th1 and CD8 T-cells, and therefore skews immune polarity in favor of Th1-based immune responses. Th1/Th2 skewing as well as increased CD8 T cell responses was confirmed in mouse models treated with ibrutinib.[^27^](#_bookmark46) Ibrutinib treatment in murine models also showed ameliorated chronic graft-versus-host disease, a condition mediated by B cell, and specific CD4+ T cell subset, due to BTK and ITK inhibition^28^.

The immunomodulatory effects of ibrutinib suggest that it can potentially be used to enhance antitumor immune response in combination with other immunotherapy modality. In a recent study performed in a mouse model with ibrutinib insensitive lymphoma, the combination of anti–PD-L1 antibody and ibrutinib suppressed tumor growth^29^.

- 1. Rationale for the proposed study

Based on the observations that 1) melanoma patients frequently exhibit evidence of Th2 polarization of immune responses, 2)Th2 polarization can compromise the ability of the immune system to eradicate melanoma cells, and 3) ibrutinib skews T cell responses toward an anti-tumor Th1 phenotype; we propose to test whether the combination of ibrutinib and pembrolizumab immunotherapy leads to an improvement in the objective response rate of advanced melanoma patients over that expected by pembrolizumab alone. In so doing, we will determine whether ibrutinib therapy drives a change in Th1/Th2 immune polarity favoring Th1 anti-tumor immune responses.

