# Test Schedule

| Treatment Cycle | Pre- registration | ≤14 days prior to  regist- ration | Active Monitoring Phase | | | | | |
| --- | --- | --- | --- | --- | --- | --- | --- | --- |
|  |  |  | Cycles 1-4^1^ | | | | Day 1 Subsequent cycles [21- day cycle] | At confirmed disease progression^2^ |
| Tests and procedures |  |  | C1D8 (±1  day) | C2D1 (±3  days) | C3D1 (±3  days) | C4D1 (±3  days) | (± 3 days) |  |
| HLA Class I Typing^R^ |  | X |  |  |  |  |  |  |
| ECOG performance status |  | X | X | X | X | X | X | X |
| History, physical exam, vital signs^3^, and weight |  | X | X | X | X | X | X | X |
| Child Pugh Score |  | X |  | X | X | X | X | X |
| Height |  | X |  |  |  |  |  |  |
| Adverse event assessment |  | X | X | X | X | X | X | X |
| Urine Pregnancy test |  | X4 |  |  |  |  |  |  |
| CBC with Differential:^5^ |  | X6 | X | X | X | X | X | X |
| Chemistry group: AST, ALT,  Bilirubin (total and direct), Creatinine, albumin, INR, LDH |  | X6 | X | X | X | X | X | X |
| TSH |  | X7 |  |  | X |  | X7 | X |
| Tumor imaging and measurement ^,8^ |  | X8 |  |  |  |  | X9 | X |
| Research blood specimens (see Section 14.0)^10,R^ |  | X | X | X | X | X | X10 | X |
| Tissue specimens (see Section 17.0)^,R^ | X11 |  |  |  |  |  | X12 | X12 |
| BRAF V600E and V600K  mutation testing |  | X |  |  |  |  |  |  |

- - 1. Cycle 1= 28 day, Subsequent Cycles=21 days.
    2. Confirmed progression is an objective status of progression on two consecutive evaluations at least 6 weeks apart.
    3. Vital signs must include blood pressure and heart rate.
    4. For women of childbearing potential only. Must be done ≤7 days prior to registration.
    5. CBC differential must include hemoglobin, platelets, absolute neutrophil count, absolute lymphocyte count, and absolute monocyte count
    6. CBC with differential and chemistry groups must be done ≤14 days prior to registration.
    7. TSH testing is to be performed ≤14 days prior to registration. And at the end of each even numbered cycle ( 2, 4, 6, 8, 10, etc.) until confirmed progression. If TSH is abnormal, T3 and free T4 testing should be performed.
    8. The initial tumor imaging (either CT or MRI, with preference for CT) will be performed ≤28 days prior to registration. The same imaging technique will be used in a patient throughout the study. If an excisional biopsy of a target lesion is to be done, baseline tumor imaging must be performed after the biopsy is done.

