    9. Imaging is to be performed at the end of Cycle 4, 6, 8, 10, and 12. If a patient has not had a confirmed disease progression after Cycle 12, subsequent scans will take place at the end of every 3^rd^ cycle of treatment thereafter (that is, at the end of Cycle 15, 18, 21 until confirmed disease progression). See Section 11.
    10. Mandatory research blood specimen will be collected at Cycle 1 Day 8 and at the beginning of each cycle for Cycles 2-4, then at the beginning of every cycle when tumor imaging is performed until confirmed progression or at treatment discontinuation if not for PD.
    11. Mandatory core needle biopsy. A newly obtained tumor biopsy is required, unless tissue is

available for research use from a prior biopsy obtained ≤90 days prior to registration.

- - 1. Mandatory tissue/biopsy is required at the time of the first disease assessment (the evaluation at the end of Cycle 4). Optional tissue/biopsy will be obtained at the time of confirmed progression. Prior to and following biopsy hold ibrutinib per section 8.4.

R Research funded (see Section 19.0)

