# Protocol Treatment

- 1. Treatment Schedule

Use actual weight or estimated dry weight if fluid retention Cycle 1 treatment = 28 days

All subsequent treatment cycles = 21 days (±3 days)

| Drug | Dose | Treatment | Retreatment |
| --- | --- | --- | --- |
| Ibrutinib | assigned at registration | PO daily (Day 1 to 28  of Cycle 1, then Day 1- 21* on subsequent cycles) | Every 21 days  (±3 days)  until confirmed progression |
| Pembrolizumab | 200 mg | IV injection on Day 8 of Cycle 1 and then Day 1 of each  subsequent cycle | Every 21 days (±3 days) until confirmed progression |

* Patients should receive a sufficient quantity of ibrutinib to last until the next scheduled treatment visit.

- 1. Determination of Maximum Tolerated Dose (MTD)
  2. Dose Escalation Scheme

| Dose level | Ibrutinib** |
| --- | --- |
| -1 | 140 mg |
| 0* | 280 mg |
| 1 | 420 mg |

* Starting dose level

** If the patient has clinical or laboratory evidence of liver failure during the treatment, then calculate the Child-Pugh score and adjust the ibrutinib dose (see Table 8.3).

NOTE: Doses will not be escalated in any individual patient.

- 1. MTD Determined

As of MCCC Amendment 6, the MTD has been determined to be Dose Level 1. Dose Level 1 will be used for the expansion cohort.

- 1. Dose Limiting Toxicities

Dose limiting toxicities (DLT) are defined to be:

| ***Toxicity*** | ***DLT Definition*** |
| --- | --- |
| Hematologic | Grade 4 ANC, Grade 4 Hgb, or PLT <25,000 |
| Renal | Serum creatinine ≥2 times baseline |
| Neurologic | ≥Grade 2 neurosensory or neuromotor toxicity |
| Other nonhematologic | ≥Grade 3 per NCI Common Terminology Criteria for Adverse Events (CTCAE) version 4.0* |

*Grade 3 rash or fever despite maximal supportive treatment(s) will be considered dose-limiting; all grade 4 rash and fever will be considered a DLT.

The maximum tolerated dose is defined as the highest dose level among those tested where at most one out of 6 patients develops a DLT prior to the start of their second cycle of treatment and the next highest dose level is such that 2 out of a maximum of 6 patients treated at this dose level developed a DLT prior to the start of their second cycle of treatment.

- 1. Dose escalation plan

NOTE: As of MCCC Amendment 6, the MTD has been determined to be Dose Level 1. A minimum of 2 or a maximum of 6 patients will be accrued to a given dose level.

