| Location for collection | Clinical phlebotomy areas in the Mayo Clinic |
| Delivery for processing | At room temperature |
|  | [name] lab, GU-323 |
|  | c/o [name] |
| Nature of processing | Ficoll centrifugation within 12 hours of receipt |
| Storage after processing | Liquid Nitrogen (PBMCs), -80 °C (plasma) |

| Samples to be collected | Peripheral whole blood (6 mL) |
| --- | --- |
| Tubes for collection | Pink top Vacutainer tubes |
| Location for collection | Clinical phlebotomy areas in the Mayo Clinic |
| Delivery for processing | At room temperature |
|  | Human Cellular Therapy Lab (Hilton 2) |
|  | c/o [name] |
| Nature of processing | Immediate processing per research experiment |
| Storage after processing | N/A |

- 1. Background and Methodology
  2. Th1/Th2 polarity assays

Frozen PBMCs from pre-treatment, post-cycle 1, and post-cycle 2 will be thawed and cultured for four hours with paramagnetic beads (Dynal, Oslo, Norway) coated with anti-CD3 and anti-CD28 antibodies (R and D Systems Minneapolis, MN). Following stimulation, cultured cells will be assessed via flow cytometry by measuring intracellular interferon gamma and interleukin (IL)-4. Brefeldin A will be purchased from Sigma-Aldrich (St. Louis, MO). Fluorochrome-labeled antibodies to IFNγ, IL-4, CD8, CD4, CD14, CD16, and CD19 will be purchased from Becton Dickinson (San Jose, CA). The stained samples will be analyzed by flow cytometry (FACScan and CellQuest software, Becton-Dickinson).

- 1. Immunophenotyping assays

The systemic impact of ibrutinib and pembrolizumab on immune cell subsets will be ascertained by immunophenotypic analysis of frozen PBMC for subsets of T helper cells, macrophages, and DC. To do this, we will label PBMC with antibodies to CD3, CD4, CD11c, CD14, C16, CD19, CD123, CD197, CD206,

CD294, HLA-DR, (BD Biosciences, San Jose, CA) and TIM-3 (R&D Systems, Inc., Minneapolis, MN). Immunophenotyping will be performed using manufacturer’s instruction in batch samples of the same patients analyzed on the same day. The stained samples will be analyzed by flow cytometry (FACScan and CellQuest software (BD Biosciences, San Jose, CA). Samples will be

assessed for the ratio of Th1 to Th2 cells (CD4+TIM-3+/CD4+CD294+), DC1 to DC2 cells (CD3-CD14-CD16-CD19-HLADR+CD11c+ to CD3-CD14-CD16- CD19-HLADR+CD123-), and M1 to M2 cells (CD14+CD197+ to

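### The stimulated Th1/Th2 polarity assay omits the Cycle 1 Day 8 sample, the only scheduled draw that can be on ibrutinib alone, so this assay can describe only the combination

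*Protocol*

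**What the plan says.** - **Polarity assay (Section 14, Background and Methodology).** Cells are stimulated and read by flow cytometry for intracellular IFN-gamma and IL-4. The time points are fixed: "Frozen PBMCs from pre-treatment, post-cycle 1, and post-cycle 2 will be thawed and cultured for four hours".
- **Dosing (Section 7, Treatment Schedule).** Ibrutinib is given "PO daily (Day 1 to 28 of Cycle 1, then Day 1- 21* on subsequent cycles" and pembrolizumab as "IV injection on Day 8 of Cycle 1 and then Day 1 of each subsequent cycle".
- **Cycle length (Section 4, footnote 1).** "Cycle 1= 28 day, Subsequent Cycles=21 days".
- **Blood draws (Section 4, footnote 10).** "Mandatory research blood specimen will be collected at Cycle 1 Day 8 and at the beginning of each cycle for Cycles 2-4", and later at imaging cycles. The Cycle 1 Day 8 column carries a window of ±1 day. Section 14 has the isolated mononuclear cells frozen in liquid nitrogen.
- **Section 14 summary table.** One pooled row, which names the polarity assays first, is marked at Cycle 1 Day 8.
- **Aims.** The rationale in Section 1 says "we will determine whether ibrutinib therapy drives a change in Th1/Th2 immune polarity favoring Th1 anti-tumor immune responses". The secondary goal in Section 2 concerns the effect of the two drugs together on Th1/Th2 polarity.
- **Immunophenotyping (Section 14).** A second Th1/Th2 measure, the ratio of CD4+TIM-3+ to CD4+CD294+ cells, is compared between the pre-treatment sample and every other sample.

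**The concern.** The staggered start gives each patient a week on ibrutinib before any pembrolizumab. The trial has no pembrolizumab-only arm, so that week is the only place within the trial where an immune change could be observed under ibrutinib alone. A shift in the IFN-gamma/IL-4 balance seen only after both drugs have been given cannot be assigned to either of them.

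The rationale for the combination rests on ibrutinib moving T-cell responses towards Th1. If the stimulated assay is run only at the listed times, a Th1 shift could be read as support for that mechanism when pembrolizumab could equally have produced it.

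**Working it through.** The point concerns timing. The plan states no figure to reproduce.

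**Study days.** Cycle 1 lasts 28 days, so Cycle 2 Day 1 is study day 28 + 1 = 29. Cycle 2 lasts 21 days, so Cycle 3 Day 1 is day 29 + 21 = 50. Pembrolizumab falls on days 8, 29 and 50. I take the post-cycle 1 and post-cycle 2 samples to be the scheduled draws at the start of Cycles 2 and 3.

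**Residual pembrolizumab.** Section 15 gives a half-life of 26 days. Assuming simple one-compartment decay, the fraction of a dose left after t days is 2^(−t/26).

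| Sample | Study day | Days since pembrolizumab | Amount left, in doses |
| --- | --- | --- | --- |
| Pre-treatment | before 1 | none given | 0 |
| Cycle 1 Day 8, before infusion (not in the assay) | 8 | none given | 0 |
| Post-cycle 1 | 29 | 29 − 8 = 21 | 2^(−21/26) = 0.57 |
| Post-cycle 2, before the third dose | 50 | 42 and 21 | 2^(−42/26) + 2^(−21/26) = 0.33 + 0.57 = 0.90 |

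The ±3-day window on the post-cycle 1 draw gives lags of 18 to 24 days and fractions of 2^(−18/26) = 0.62 to 2^(−24/26) = 0.53. If either draw followed that day's infusion, exposure would be higher. So 0 of the 2 on-treatment polarity samples are free of pembrolizumab, at any point in the window.

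**What Day 8 would add.** A sample taken before the infusion on Day 8 follows 7 daily ibrutinib doses (8 if that day's capsules have been taken) and 0 pembrolizumab doses. No other scheduled draw can do this.

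**Whether the Day 8 draw is protected.** With pembrolizumab on Day 8 as scheduled, the window allows three draw days:

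- Day 7: before the infusion.
- Day 8: before or after, because the order is not stated.
- Day 9: after.

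The ibrutinib-only status of the sample is therefore possible but not assured. This also affects the surface-marker ratio, which already uses the Day 8 sample.

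**Number of patients.** Section 16 gives 6 already treated at the 420 mg level plus 10 in the expansion, so at most 16 contrasts at that dose.

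**The case against.** - **The listed goal is the combination.** This stands. Pre-treatment against post-cycle 1 and post-cycle 2 addresses the secondary goal in Section 2. The attribution to ibrutinib appears only in the rationale. A reader might infer that the assay fails its goal, but the documents do not support that.
- **Another assay reads Day 8.** This stands too. A reader might infer that the trial cannot look at ibrutinib alone, or that the lead-in week goes unused. The immunophenotyping ratio covers that sample, and the plasma cytokine assays share the pooled row marked at Day 8. Nor does the protocol rank the stimulated assay above the surface-marker ratio.
- **The summary table may only be a collection schedule.** Fair. The pooled row is also marked for later draws that the polarity assay does not use, so the mark at Day 8 does not prove an intention to run it there. The two places still leave the question open, and the methods text fixes a list without Day 8.
- **Day 8 would not test ibrutinib.** Correct. It would be an uncontrolled before-after comparison in a small cohort, and Section 16 calls the laboratory correlates exploratory.
- **The window counts little.** Partly right. The ±1 day applies to the whole visit, so draw and infusion may move together. The three permitted days do not mean that one draw in three would follow the infusion. Laboratory instructions not seen here may settle the order. The protocol itself does not.

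**Conclusion.** The point holds for the stimulated polarity assay. Both of its on-treatment samples follow pembrolizumab, with about 0.57 and 0.90 of a dose still present on the stated half-life under one-compartment decay. The conclusion itself needs only the dosing order, not the decay model. This assay can describe the combination effect and cannot inform the rationale's statement about ibrutinib.

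The surface-marker ratio can give a Day 8 reading, but neither that reading nor an added polarity reading is secure as ibrutinib-only while the draw may follow the infusion. The matter is a cheap improvement to a laboratory correlate. The maximum tolerated dose, the response endpoint and the sample size are untouched.

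**What to change.** - In Section 14, reconcile the summary table with the methods text by adding Cycle 1 Day 8 to the polarity-assay time points: pre-treatment, Cycle 1 Day 8, post-cycle 1 and post-cycle 2.
- In Section 4 and the Section 14 table, state that the Day 8 research blood is drawn before the first pembrolizumab infusion.
- Exclude any Day 8 sample drawn after that infusion from the ibrutinib-only contrast.
- Report Day 8 minus pre-treatment as an exploratory, uncontrolled ibrutinib-only contrast, and the later samples as the combination effect. The number at 420 mg is at most 16. It falls if samples are excluded or if the expansion safety checks lower the starting dose, as Section 16 allows.

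The cost is one more assay run per patient on cells already banked, and a line on draw timing. No new visit or blood draw is needed, and patients already treated can be included where Day 8 cells remain in storage.

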CD14+CD206+). Changes in Th1/Th2 ratio, DC1/DC2 ratio, and M1/M2 ratio between the pre-treatment sample and each other sample will be used to determine the systemic impact of treatment on immune cell subsets.

- 1. Plasma cytokine assay

We will profile the plasma cytokine changes as a result of vaccine administration. The BioRad human 27-plex cytokine panel will be used (Cat # 171-A11127, Bio-Rad, San Diego CA) for the measurements of plasma concentrations of IL-1β, IL-1rα, IL-2, IL-4, IL-5, IL-6, IL-7, IL-8, IL-9, IL-10, IL-12(p70), IL-13, IL-15, IL-17, basic FGF, eotaxin, G-CSF, GM-CSF, IFN-γ,

IP-10, MCP-1, MIP-1α, MIP-1β, PDGF, RANTES, TNF-α, and VEGF. The

assay will be performed as per the manufacturer’s directions. Briefly, 100 mcL of Bio-Plex assay buffer will be added to each well of a MultiScreen MABVN 1.2 um microfiltration plate followed by the addition of 50 mcL of the multiplex bead preparation. Following washing of the beads with the addition of 100 mcL of wash buffer, 50 mcL of the samples or the standards will be added to each well and incubated with shaking for 30 minutes at room temperature. The plasma (1:3 dilution) and standards will be diluted using the Bio-Plex human serum diluent kit and plated in duplicate. Standard curves will be generated with a mixture of 27 cytokine standards and eight serial dilutions ranging from 0-32,000 pg/mL. The plate will then be washed 3 times followed by incubation of each well in 25 mcL of pre-mixed detection antibodies for 30 minutes with shaking.

The plate will further be washed and 50 mcL of streptavidin solution were added to each well and incubated for 10 minutes at room temperature with shaking. The beads will be given a final washing and resuspension in 125 UL of Bio-Plex assay buffer. Cytokine levels in the sera will be quantified by analyzing 100 mcL of each well on a Bio-Plex using Bio-Plex Manager software version 4.0. Normal values for plasma cytokine concentrations were generated by analyzing 30 plasma samples from healthy donors (blood donors at the Mayo Clinic Dept. of Transfusion Medicine). A set of five normal plasma samples (standards) will be run alongside all batches of plasma analysis in this study. If the cytokine concentrations of the “standard” samples differ by more than 20%, results will be rejected and the plasma samples re-analyzed.

- 1. Tetramer assays

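### The DC2 gate is printed as CD123-negative, so it overlaps the DC1 gate and leaves out CD11c-CD123+ cells; the DC1/DC2 ratio does not contrast two distinct subsets

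*Protocol*

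**What the plan says.** Protocol Section 14 (Body Fluid Biospecimens), Background and Methodology, Immunophenotyping assays, defines three ratios from frozen blood mononuclear cells.

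- **Th1/Th2:** "ratio of Th1 to Th2 cells (CD4+TIM-3+/CD4+CD294", with a plus sign after the last marker. Each side has its own positive marker.
- **DC1/DC2:** "DC1 to DC2 cells (CD3-CD14-CD16-CD19-HLADR+CD11c+ to CD3-CD14-CD16- CD19-HLADR+CD123", with a minus sign and closing parenthesis after CD123.
- **M1/M2:** "M1 to M2 cells (CD14+CD197+ to" CD14-positive, CD206-positive cells. Again each side has its own positive marker.

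The antibody list includes both CD11c and CD123: "label PBMC with antibodies to CD3, CD4, CD11c, CD14, C16, CD19, CD123, CD197, CD206", followed by further markers. No other definition of DC2 appears in the protocol.

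The section then fixes the use of the ratios: "Changes in Th1/Th2 ratio, DC1/DC2 ratio, and M1/M2 ratio between the pre-treatment sample and each other sample will be used" to judge how treatment affects immune cell subsets systemically.

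**The concern.** A ratio of two cell subsets is readable when numerator and denominator are different cells. Here the two gates start from the same parent population and each adds one condition on a different marker. A cell that is CD11c-positive and CD123-negative satisfies both.

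The CD11c-negative cells that the CD123 antibody stains satisfy neither gate. If they are the intended DC2 population, the readout is blind to them: they could fall or rise sharply after treatment and the reported DC1/DC2 change would not show it. A real rise in DC1 would also be partly cancelled, because the same cells enter the denominator. A laboratory that follows the text could therefore report little or no shift when one had occurred.

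**Working it through.** The protocol gives no cell frequencies and no figure for this readout, so there is nothing to reproduce. The check is set algebra on the printed gates, with assumed counts for illustration only.

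**Notation.** Split the lineage-negative, HLA-DR-positive cells into four groups:
- a = CD11c+CD123+
- b = CD11c+CD123-
- c = CD11c-CD123-
- d = CD11c-CD123+

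**Gates as printed.** DC1 = a + b. DC2 = b + c. Ratio = (a + b)/(b + c).

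**1. Cells left out.** Group d does not appear, so no change in d can move the ratio. With a CD123-positive DC2 gate the ratio would be (a + b)/(a + d). Assume a = 2, b = 50, c = 20:

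| d | As printed, (a+b)/(b+c) | CD123+ gate, (a+b)/(a+d) |
| --- | --- | --- |
| 28 | 52/70 = 0.743 | 52/30 = 1.733 |
| 14 | 52/70 = 0.743 | 52/16 = 3.25 |
| 56 | 52/70 = 0.743 | 52/58 = 0.897 |

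**2. Overlap.** With the same counts, 50/52 = 96% of the DC1 gate also lies in the DC2 gate, and 50/70 = 71% of the DC2 gate is DC1 cells.

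**3. Ceiling.** If a = 0, the ratio is b/(b + c), which can never exceed 1. It can exceed 1 only if a is larger than c.

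**4. Damping of a change in DC1.** Take a = 0 and double b. The written ratio is multiplied by [2b/(2b + c)] / [b/(b + c)] = 2(b + c)/(2b + c). For two separate subsets the factor would be 2.0. With b = 60:

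| c | Before | After doubling b | Factor |
| --- | --- | --- | --- |
| 20 | 60/80 = 0.75 | 120/140 = 0.857 | 1.14 |
| 60 | 60/120 = 0.50 | 120/180 = 0.667 | 1.33 |
| 200 | 60/260 = 0.231 | 120/320 = 0.375 | 1.63 |
| 600 | 60/660 = 0.091 | 120/720 = 0.167 | 1.83 |

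So damping is severe when double-negative cells are few and slight when they are many.

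**5. Comparison with the other gates.** The distinguishing markers of the six subsets are TIM-3+ (Th1), CD294+ (Th2), CD11c+ (DC1), CD123- (DC2), CD197+ (M1) and CD206+ (M2). DC2 is the only one with a negative marker.

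**The case against.** **The protocol never says that DC2 cells are CD123-positive.** This stands. That reading is an inference from the pattern of the other five subsets. The overlap and the exclusion of group d do not depend on it; they follow from the printed gates.

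**CD123 being in the panel proves nothing.** This also stands. A negative gate needs the antibody too, and CD3, CD16 and CD19 are in the panel and used in these gates only for exclusion. The panel is compatible with a sign error but does not establish one.

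**The other ratios overlap as well.** A TIM-3+CD294+ cell or a CD197+CD206+ cell would count on both sides, so the section uses shorthand phenotypes throughout. That is correct, and strict exclusivity is not demanded elsewhere. The DC case differs in kind: the overlap is not confined to double-positive cells but takes in every DC1 cell that lacks CD123.

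**Stronger readings that the documents do not support.** A reader might infer that the ratio hardly responds to DC1. That depends on the number of double-negative cells, which the documents do not give; the factor runs from 1.14 to 1.83 over the range shown. A reader might also infer that the ratio cannot track DC2 cells at all, but that takes DC2 to be CD123-positive as settled. Finally, one might assume that existing data can simply be re-gated. The protocol does not say that flow files are kept, or that CD11c and CD123 are stained in the same tube.

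**The readout is minor.** Agreed. DC1/DC2 is not named in the Goals section, and Section 16 treats laboratory correlates as exploratory and hypothesis-generating.

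**Conclusion.** The point holds as a defect in a stated assay rule. Followed literally, the DC1/DC2 ratio counts CD11c+CD123- cells on both sides, cannot respond to CD11c-CD123+ cells, and cannot exceed 1 if no cells are double-positive. These statements need only the printed gates. The size of the damping for DC1 rests on assumed counts and can be quoted only as a range.

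A sign error, CD123- for CD123+, is the likely explanation. A text-reading fault is unlikely, since the other plus and minus signs in the same string came through. The laboratory still has to confirm what was intended.

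The consequence is confined to one exploratory correlative readout. The maximum tolerated dose, the response endpoint and the sample size are unaffected, so this is a low-severity correction.

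**What to change.** 1. Ask the laboratory which DC2 gate was intended and which was actually used.
2. Correct the DC2 definition in the immunophenotyping section, probably to CD123-positive, so that DC1 and DC2 are distinct populations. Changing the sign alone leaves only the double-positive cells shared: with the assumed counts, 2 of 30 cells in the DC2 gate, against 50 of 70 as printed.
3. If CD11c and CD123 are stained in the same tube, remove that remainder too, by adding a CD123-negative condition to DC1 and a CD11c-negative condition to DC2.
4. Apply one definition to every sample, including pre-treatment samples, so that changes from baseline are comparable.

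The text change is one line, and both antibodies are already in the panel. Data already acquired can be re-gated only if the flow files were kept, which the protocol does not state. If they were not, results obtained with the printed gate should be labelled as such and not pooled with results from the corrected gate.
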